##### Objective 4: Preliminary indications of associations

The preliminary indications of associations between outcome variables will be facilitated using correlation and association measures (Pearson's product–moment correlation coefficient for numerical outcomes) (uncorrected chi-squared test for association and/or Fisher's exact test for categorical outcomes). Liberal confidence intervals (e.g. 80%, 90%) will be applied.

### Ethics

A detailed information letter will be provided to each participant. This letter will explain the nature of the study and what participation would involve. After the participant is given time to clarify anything about study participation, the principal researcher will obtain each participant's consent. It will be made clear that data will be retained in an anonymous form. Participants are free to withdraw at any time during the study. Data will be safely stored in an encrypted computer, and only the principal researcher will have access to this data. This is per data protection directives (GDPR EU 2016/679). The protocol was approved by the University of Malta Ethics Committee (UNIQUE FORM ID: 3756_191119) and the Malta Health Ethics Committee (HEC03 CT01/20).

## Discussion

This study aims to evaluate a pilot study of a preventive cardiology program designed to promote risk reduction in a potential risk group. Issues of feasibility in the study design need to be tested before conducting a larger-scale randomised controlled trial [52]. The testing requires determining acceptability, estimating participants' recruitment and retention rate, evaluating the Intervention's operational strategy, and estimating the sample size needed for a full-scale study. The Medical Research Council framework guidance reports that a pilot study must be a scale model of the planned full-scale Intervention and must identify and address any issues [52].

Having access to a cardiovascular risk assessment (Opportunity) and being able to understand heart risk and ways to change risk (Capability) might increase motivation to modify present risks (Fig. 3). The key determinant is motivation; however, motivation alone is not sufficient as individuals still need to understand their risk, develop the skills required to reduce it, and have good access to cardiovascular risk assessment and follow-up. In this way, the interaction between Capability, Opportunity, and Motivation could be pivotal in supporting and bringing about the desired behaviour changes [43]. Figure 3 shows the application of COM-B in the CRISO program to modify risk. This approach was adopted from Michie et al. [53].

**Fig. 3 Fig3:**
[figure not shown]
Application of COM-B in the CRISO program to modify risk

### Strengths and limitations

The Intervention's delivery and all measurements will be performed by the same researcher, producing more consistency. A guide was developed to support the fidelity of the Intervention. A randomly chosen set of 10 audio-recorded sessions will be assessed against an intervention guide. A randomised controlled design was selected as it would allow testing for potential intervention effectiveness. This can provide supportive data for preventive program development to be tested on a larger sample future RCT. Part of the study will include conducting interviews, which will help us understand participants' views about the Intervention's implementation and acceptability. This data will allow valuable information on what components are useful to deliver the intervention and support risk factor modification in potential risk groups. The internal pilot phase will dictate any modifications needed in the intervention. However, the data collected for this purpose is proposed in the final efficacy analysis, disregarding that part of the data which came from a pilot phase.

### Future research opportunities

The CRISO study has considered the possibility of future studies. If this study were to establish feasibility, a large scale, randomised controlled trial will be designed and implemented, with the possibility to facilitate the assessment of countrywide effects. This study would be the first in Malta to test the effectiveness of an evidence-informed intervention to support first-degree relatives to modify risk.

As the study is to recruit first-degree relatives, these would generally have a combination of clinical, biochemical, and genetic risk factors [54, 55]. In the CRISO study, intervention participants who are found to have alarming parameters (atherogenic lipid profile, obesity) will be asked to consent for blood genetic testing at a 1-year time point. Having such samples will open another route for future research to determine if there is an association between genetic risk score (a combination of variants) in those with alarming parameter/s (phenotypes—traditional risk factors). If an association is found, this may suggest that conventional risk should be combined with genetic risk, which may give the total potential risk. This study might further refine preventive cardiology.

### Counterbalancing for confounding factors and bias

There are several possible interacting variables: age, health literacy, educational levels, isolation, employment, sex, psychometric scales, time of the cardiac patient event, and family clustering effects. These multiple variables make it rather complex to decide on stratified sampling. Additionally, as the sample solely depends on the recruitment process, an element that still needs to be tested, it was decided not to stratify at this phase.

The chosen method to generate the allocation sequence should produce comparable groups. However, due to a lack of resources, allocation concealment is not possible. This study is single-blinded, where participants will only be informed about the aim of the study but not about being part of an intervention or control group. However, the researcher will be aware of which participants have been allocated to the intervention group. Thus, there is a risk of performance and detection bias. An independent person from the study will perform group allocation. Also, group allocation will take place before the baseline risk assessment. Using these methods will avoid any attempt to allocate participants to the Intervention according to their risk profile. This step is necessary when the study's nature does not allow proper blinding [56].

Numbers of the total sample randomised, those lost to follow-up, and reasons for withdrawal will be recorded for each group. The risk of attrition bias will be minimised by carrying forward the last observation. This method will keep the groups balanced if there is a loss to follow-up/missed measuring time points.

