### Primary outcomes

#### Feasibility

Feasibility will be ascertained by evaluating the recruitment and intervention processes. The study's feasibility requires that the Intervention be effectively carried out amongst an adequate number of first-degree relatives over 2 years. The assessment of the feasibility of the recruitment process will include records of the number of first-degree relatives:
Reached via patients/ video clip (link to video clip)/ poster (link to poster)/ study participants/ clinician,Who expressed interest in the study,Who are potentially eligible, with reasons for ineligibility,Who agreed to participate in the trial,Lost to follow-up (retention and drop-out rate),

Furthermore, the assessment of the feasibility of the Intervention will include the time taken to:
Complete the cardiovascular risk assessment,Deliver the Intervention (in-person session and telephone sessions).

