### Sampling frame

About seven acute coronary syndrome (ACS) patients are admitted to the acute general hospital per week, including unstable angina, non-ST and ST-segment elevation ACS. About 40% will present with premature ACS [4]. Maltese individuals who are 30 years and older often have quite extensive families. Across 52 weeks (1 year), logistically, if every patient informs their relatives, this would amount to over 100 eligible participants. Since there are no records concerning the recruitment uptake and attrition rate, we will dedicate two years for recruitment and data collection. A sample of 100 participants should be adequate to prove that the process is viable. As the pilot study is not expected to be powered to detect differences between groups, there is no universally accepted calculation for the pilot study sample size [38]. If a meaningful group difference is unknown and the pilot study is intended to establish an effect size for sample size calculation, it is recommended to have 30 to 40 participants recruited in each group. Recommendations for feasibility studies propose a minimum of 30 participants per arm to estimate parameters for future sample size calculations [39, 40]. Ultimately, the sample size decision for a pilot RCT must also consider the research timeline, human resources and costs, and the research objectives [40, 41].

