#### Group randomisation

Before the baseline/pre-intervention evaluation, approximately 100 participants shall be randomly allocated to one of the two groups:
The intervention group shall consist of 50 participants. Participants in this group will have one face-to-face session (evaluation of modifiable risk factors, 2-way risk factor communication, education, and individualised counselling to set up a cardio-protective documented plan) followed by weekly telephone-based cardio-protective reinforcement sessions for up to 12 weeks.The control group shall consist of 50 participants. Participants will have one face-to-face session of verbal lifestyle advice only.

Block randomisation will be applied to balance out the sample size between the intervention and control groups. An opaque sealed envelope technique, using block randomisation with blocks of size four, will be implemented for this study. This method will allow an equal chance of being allocated to one of the two groups and ensure that near-equal numbers are assigned to each group, minimising the risk of group imbalances and allocation bias.

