#### Secondary outcome analysis

##### Objective 3: Estimates of effect and preliminary evidence of efficacy

The likely range of effects will be estimated using liberal confidence intervals. Preliminary estimates of intervention efficacy will be established via hypothesis tests with liberal alpha values (e.g. 0.15, 0.2). Numerical outcomes measured on an interval level, and numerical outcomes measured on an ordinal scale that can be considered approximate to interval level, will be assessed using independent samples t tests. Categorical data will be assessed using the chi-squared test for association.

Intention-to-treat analysis will be used to test for the differences between the two groups at the endpoint [50]. Intention-to-treat analysis is considered the gold standard method for evaluating a new intervention. This method includes all study participants whether or not they have completed the study program and will preserve the randomisation process as it keeps the groups balanced in their number of participants in case of any drop-outs, thus minimising biases [51].

Risk ratios (RRs) will be generated for selected outcome variables, dichotomised as necessary, from proportions of participants meeting particular criteria (e.g. control of blood pressure) in the control and intervention groups.

Effect sizes such as Cohen's d statistics will be calculated for each outcome measure and presented alongside parameter estimates in each group and associated confidence intervals. These, in conjunction with other statistics derived from the pilot analysis, may be used to estimate sample size for a subsequent follow-up RCT [38].

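### Several relatives of one index patient are likely to enrol and the protocol names family clustering, yet it fixes individual allocation and tests that treat all participants as independent

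*Protocol article*

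**What the plan says.** **Recruitment.** The Sampling frame section states that "Maltese individuals who are 30 years and older often have quite extensive families" and that "if every patient informs their relatives, this would amount to over 100 eligible participants". The Feasibility section lists the routes by which relatives may be reached as "Reached via patients/ video clip (link to video clip)/ poster (link to poster)/ study participants/ clinician", so enrolled participants can bring in further relatives. The Recruitment section makes index patients a source of participants, alongside posters and social media.

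**Allocation.** Under Group randomisation, "approximately 100 participants shall be randomly allocated to one of the two groups", "using block randomisation with blocks of size four". The unit is the person. Nothing in the article limits enrolment to one relative per index patient or keeps a family in one arm.

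**Recognition.** The section on counterbalancing for confounding and bias names "time of the cardiac patient event, and family clustering effects" among possible interacting variables. The response to the whole list is that "it was decided not to stratify at this phase".

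**Analysis.** Under Objective 3, numerical outcomes "will be assessed using independent samples t tests" and categorical outcomes go to a chi-squared test. Per-arm estimates are to carry confidence intervals, and the effect sizes may feed the sample size of a later trial. Objective 4 uses Pearson correlations, or chi-squared or Fisher tests, with 80% or 90% intervals. The covariate adjustment offered under the sociodemographic questionnaire is triggered by baseline imbalance, and family membership is not among the items listed there.

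**The concern.** Siblings, or the offspring of one patient, may share diet, smoking habits, activity and inherited risk, so their outcomes may be correlated. Deciding not to stratify does not deal with this. Stratification balances a covariate between arms; it neither keeps relatives together nor allows for their correlation. Two things are at stake.

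- **Precision.** Intervals that assume independence are wrong by an amount and in a direction that depend on the estimate: whole-cohort summary, per-arm mean, correlation or between-arm difference.
- **The planning value of the pilot.** Relatives in opposite arms may share the written plan and goals, and may work out which group each is in, which the single-blind design tries to prevent. The observed effect size would then be diluted. Nor does the analysis described give a family ICC or family-size distribution for designing the definitive trial.

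**Working it through.** **Inputs from the document.** 100 participants, 1:1, blocks of four; seven acute coronary syndrome admissions a week, about 40% premature; two years for recruitment and data collection; liberal alpha of, for example, 0.15 or 0.20 (taken as two-sided).

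**Assumptions (not in the document).** Relatives per family m, ICC, share of participants with an enrolled relative s, and uptake of the intervention effect by a control relative u.

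**1. Recruitment basis.** 7 × 52 × 0.40 = 145.6 premature cases a year, which agrees with the claim of over 100 eligible relatives. N = 100 rests on a pilot rule of thumb, with no effect size or power behind it to reproduce.

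**2. Chance that a pair is split.** Same block of four: once one relative is placed, two of the three remaining slots belong to the other arm, so 2/3. Different blocks: 1/2. Simulation gave 0.67 and 0.50.

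**3. Whole-cohort means and proportions.** True SE / naive SE = √(1 + (m − 1) × ICC). With everyone in pairs:
- ICC 0.1: √1.1 = 1.05
- ICC 0.3: √1.3 = 1.14

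The article states no intervals for these summaries, so this applies to any that are attached.

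**4. Objective 4 correlations.** For two otherwise unrelated variables the factor is about √(1 + (m − 1) × ICC of x × ICC of y). With everyone in pairs:
- both ICCs 0.1: √1.01 = 1.005
- both ICCs 0.3: √1.09 = 1.044

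So the shortfall is about 0.5 to 4%.

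**5. Per-arm and between-arm estimates.** Simulation of 100 people in blocks of four, with a t test ignoring family and 6,000 runs per scenario. Ratios are true variance over naive variance; the last column is the actual error of the between-arm test at nominal 0.20.

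| Family size, ICC | Order of enrolment | Per-arm ratio | Between-arm ratio | Error |
|---|---|---|---|---|
| 2, 0.2 | scattered | 1.12 | 1.01 | 0.199 |
| 2, 0.2 | together | 1.09 | 0.96 | 0.196 |
| 2, 0.5 | scattered | 1.23 | 0.99 | 0.195 |
| 2, 0.5 | together | 1.14 | 0.83 | 0.164 |
| 4, 0.5 | scattered | 1.75 | 1.02 | 0.206 |
| 4, 0.5 | together | 1.54 | 0.50 | 0.076 |

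If only half of participants come as pairs with ICC 0.2, the per-arm ratio falls to 1.00–1.04.

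**6. Dilution.** Share of controls with a relative in the intervention arm = s × (1/2 to 2/3). Share of effect lost = that × u. Inflation of the next trial, if sized on the diluted effect = 1 / (1 − loss)². With u = 0.30:
- s = 0.20: loss 0.03 to 0.04; 1/0.97² = 1.06 to 1/0.96² = 1.09
- s = 0.40: loss 0.06 to 0.08; 1/0.94² = 1.13 to 1/0.92² = 1.18
- s = 1.00: loss 0.15 to 0.20; 1/0.85² = 1.38 to 1/0.80² = 1.56

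**The case against.** **The number of relatives per family is unknown.** This stands. At 145.6 cases a year, two years give about 291 index patients, so 100 participants is about 0.34 per index patient, and posters and social media also recruit. A reader might infer that siblings will be split and will contaminate the control arm. The document makes shared families likely but gives no count, and says nothing of how much of a personalised session, plan and 12 calls a relative could pass on.

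**A large dilution figure needs near-universal pairing.** This also stands. An inflation of 38% follows if half of controls have a relative in the intervention arm and take up 30% of the effect. With pairs split at 1/2 to 2/3, that needs 0.5 ÷ 2/3 = 75% to 0.5 ÷ 1/2 = 100% of participants to enrol in pairs.

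**The treatment comparison is not anti-conservative.** Correct. A reader used to cluster trials might infer that the between-arm interval is too narrow. Under individual allocation it is not: the simulated error stays near 0.20 or falls below it.

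**Randomising by family now would carry its own risk.** If the first relative's envelope fixed the arm for the rest, later relatives' arms would be known before consent. The principal researcher obtains consent, and the study investigator delivers the intervention, assesses outcomes and knows the allocation. Selective enrolment could follow. Recruitment began in September 2020, so the trial would also become a mixed design.

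**This is an unpowered pilot, and a condensed article may leave analysis detail elsewhere.** Only partly an answer. Feasibility and acceptability are the primary objectives, but the article itself raises clustering, responds only by not stratifying, and fixes tests that ignore it. Its Discussion lists sample-size estimation for the full trial among the pilot's tasks, and low power does not excuse a biased planning input.

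**Conclusion.** The point holds in a limited form and should be acted on. The document names family clustering, allocates individuals and prescribes tests that assume independence. For positively correlated relatives, the largest distortion for a given family structure is in whole-cohort means and proportions, within the 1.05 to 1.14 range above for pairs. Per-arm intervals are affected less, correlations only slightly, and the between-arm interval is about right or too wide. All of this shrinks as fewer participants share a family and grows with larger families or higher ICC.

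Dilution of the effect size is a plausible consequence, not a demonstrated one. Its size cannot be stated without the share of participants who have an enrolled relative and the uptake by controls. The document does not support presenting contamination as certain, quoting one inflation figure for the next trial, or calling the treatment-effect intervals too narrow.

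**What to change.** 1. Record an index-patient (family) identifier for every participant, including those already enrolled.
2. Under Objectives 3 and 4, replace the independence-based tests with models that have a family random intercept, or with family-clustered standard errors. Treat intervals for whole-cohort and per-arm summaries in the same way.
3. Report the number of relatives per family, how many families are split across arms, and the ICC with its interval. With 25 pairs the ICC's standard error would be near 0.2, so it is a rough guide only.
4. Add a sensitivity analysis that leaves out families split across arms.
5. Leave the current allocation unchanged. For the definitive trial, consider allocating by family, with all interested relatives listed before the envelope is opened. The analysis must then match: in simulation, a t test ignoring family under whole-family allocation rejected at 0.24 (pairs, ICC 0.2) to 0.43 (four per family, ICC 0.5) against nominal 0.20.

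The cost is one data field, a few sentences of analysis text and slightly more analysis work. Some intervals become a little wider.

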Blood biochemicals (lipids, HbA1c) will be analysed using the Roche COBAS analyser, while TFT will be analysed using the Siemens ADVIA Centaur analyser. Both analysers are closed systems, and the kits that will be used are only those provided by Roche and Siemens, respectively.
Physiological measures

Resting physiological measurements will be measured using an Omron™ blood pressure monitor, measured two to three times by auscultation, and an average will be taken as the final measurement. Heart rate shall be measured manually using the radial pulse. For both measurements, the first measurement shall be monitored after a 10-min seated rest, repeated 10 min after, and then again at the end of the session. Blood pressure will be measured in both arms.
Anthropometric measures

Anthropometric measurements will be measured using a SECA scale with a height gauge. Numerous steps will be taken to avoid measurement errors. Weight will be taken to the nearest 0.1 kg and both measurements recorded twice. Recording of the waist circumference will be recorded while the participant is standing. A non-elastic measuring tape will be placed at the midpoint between the iliac crest and the lowest rib and at the umbilicus level. This measurement will be taken at the end of expiration.
Heart Age

Heart Age will be calculated after obtaining the following parameters: age, sex, systolic blood pressure, cholesterol, smoking status, weight, and height. The parameter data obtained will be inputted into the online calculator to generate a score. This score will allow for the observation of changes in global risk [35].
Health literacy

The Health Literacy Questionnaire (HLQ) has nine scales in total [36, 37]. We decided to select those scales which we think are relevant to the Intervention. The questions will not be amended as they are validated in the way they are. However, the researcher shall tell the participant that the questions asked are about their heart health.

The scales selected are: scale 1, Feeling understood and supported by healthcare professionals; scale 2, Having sufficient information to manage health; scale 3, Actively managing health.

The selected scales' response options range from 1 to 4, with the scoring as follows: 'strongly disagree’ = 1, 'disagree’ = 2, 'agree' = 3, 'strongly agree’ = 4. The total score is calculated for all the questions on that scale and divided by the number of items.

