#### Blinding and allocation concealment

Awareness of being part of the intervention group may result in participants behaving differently to what they otherwise might do. Group awareness could have implications for the study's internal and external validity. The participants were informed about the aim of the study; however, not about to which group they have been allocated. Furthermore, participants will be allocated by an independent person from the study, and allocation will occur before the baseline/pre-intervention risk evaluation. Due to resource limitations, the study investigator will deliver the Intervention and assess the outcomes, therefore making part of the blinding impossible. However, blinding will be imposed on the data analyst.

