**Table 4 Tab4:**
[figure not shown]
Data collection points

✓* Intervention delivered 2-3 days after T0 for blood results to be issued

✓** Control delivered 2-3 days after T0 for blood results to be issued

Telephone reinforcement sessions following the combined risk communication and counselling session will also be used. In total, participants receive one in-person session and 12 telephone calls (occurring between weeks 1 and 12).

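### Participants are described as blinded, but the content of the arms probably reveals allocation, so participant blinding cannot be relied on for the self-reported outcomes

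*Protocol article*

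**What the plan says.** Two sections of the protocol article make the claim. Blinding and allocation concealment says: "The participants were informed about the aim of the study; however, not about to which group they have been allocated". Counterbalancing for confounding factors and bias turns this into a label: "This study is single-blinded, where participants will only be informed about the aim of the study". The rest of that sentence says that their arm is not disclosed to them.

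The same article describes arms that look different from the inside:

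- **Intervention:** "In total, participants receive one in-person session and 12 telephone calls (occurring between weeks 1 and 12"). Group randomisation and Intervention arm add a documented plan and an electronic report that is updated at 6 and 12 months.
- **Control:** "Participants will have one face-to-face session of verbal lifestyle advice only".

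Diet (MEDAS), physical activity (RAPA) and three Health Literacy Questionnaire (HLQ) scales are questionnaire outcomes. One of the HLQ scales is "scale 1, Feeling understood and supported by healthcare professionals". The investigator who delivers the intervention also assesses the outcomes, and only the data analyst is masked. Counterbalancing for confounding factors and bias admits a risk of performance and detection bias, but derives it from the researcher's knowledge of allocation.

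**The concern.** The article itself names the hazard: "Awareness of being part of the intervention group may result in participants behaving differently to what they otherwise might do". Its answer is not to disclose the arm. That works only if the arm cannot be recognised from what is delivered, and here it probably can be.

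The stated hypothesis concerns lifestyle improvement. Diet and activity are reported by people who may know they are in the supported arm, in a study where the assessor is also the person who coached them. A wish to report progress would shift these scores without any change in behaviour. Objective 3 tests such outcomes at liberal alpha levels and says that effect sizes may help to size a later trial. A reader who accepts the single-blind label would take such a shift as preliminary evidence of effect. An inflated Cohen's d would also leave the next trial too small, because required sample size varies as 1/d².

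**Working it through.** The plan gives no figure on this point to reproduce. The check sets the sections side by side and then illustrates the possible consequence.

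**1. Contacts.** Intervention: 1 in-person session + 12 calls = 13. This is a planned maximum, since Group randomisation says the weekly calls run for up to 12 weeks. Control: 1. Follow-up adds assessments at baseline, 6 and 12 months in both arms, giving 13 + 3 = 16 against 1 + 3 = 4. The difference is 12 either way.

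**2. What a participant can see.** Someone told the study's aim, who then receives a documented plan, an electronic report and weekly calls, has good grounds to conclude that they are in the programme arm. A control participant has weaker grounds: they receive real advice on smoking, diet and activity and may not know what the other arm gets.

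**3. Which outcomes are exposed.**

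- Exposed to participant reporting: MEDAS (0 to 14), RAPA (0 to 10) and the three HLQ scales.
- Partly protected: smoking, because a report of having stopped is checked by expired carbon monoxide.
- Not self-reported, but measured by the unblinded researcher: blood pressure, waist circumference and body mass index. Heart Age combines measured inputs with smoking status.
- Read on laboratory analysers: lipids and HbA1c.

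**4. What the admitted bias covers.** The risk is attributed to the researcher knowing the allocation. The participant route is left out because participants are described as blinded.

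**5. Illustration.** Inputs from the article: 50 per arm and alpha of 0.15 or 0.20. Assumptions: no true effect, no attrition, and a reporting bias b (in SD units) favouring the intervention. The article gives no value for b, so a range is shown.

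Standard error of the standardised difference = √(2/50) = 0.20.

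P(significant, two-sided) = Φ(b/0.20 − z) + Φ(−b/0.20 − z), with z = 1.440 for alpha 0.15 and 1.282 for alpha 0.20.

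For b = 0.2 at alpha 0.15: Φ(1 − 1.440) + Φ(−1 − 1.440) = 0.330 + 0.007 = 0.337.

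| Assumed bias (SD) | alpha 0.15 | alpha 0.20 |
|---|---|---|
| 0 | 0.150 | 0.200 |
| 0.1 | 0.200 | 0.255 |
| 0.2 | 0.337 | 0.400 |
| 0.3 | 0.526 | 0.589 |
| 0.5 | 0.856 | 0.889 |

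The table shows how sensitive the planned tests would be to such a bias. It does not estimate the bias.

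**The case against.** The best defence is that the article is already candid. It says that part of the blinding is impossible, raises group awareness as a threat to validity, and admits performance and detection bias. The single-blind sentence also explains what it means by the term, and no analysis section relies on it. The primary objectives are feasibility and acceptability, the affected outcomes are secondary in an unpowered pilot, and arms that participants can tell apart are usual in behavioural trials. All of this is true and limits the weight of the point. It does not remove the point, because the participant route to bias is still described as closed.

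Four stronger readings are tempting, and the document does not support them:

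- *That participant blinding does not exist at all.* The allocation is withheld. Ethics says of the information letter, "This letter will explain the nature of the study and what participation would involve", but the letter is not shown, so it cannot be assumed to describe both arms. Nothing shows that controls know about the calls.
- *That HLQ scale 1 largely measures the study contact.* This would rest on the scale's title. The items are not shown, the scale is one of three scored separately, and professional contact is an intended mechanism of the programme. It may partly reflect that contact; more cannot be said.
- *That the effectiveness claim rests mainly on self-report.* Potential intervention effectiveness also names lipids, blood pressure, waist circumference, body mass index and Heart Age, and ties its significance criterion to these.
- *That the researcher administers the questionnaires by interview.* The article does not say how they are completed. A condensed article may leave that to the full protocol, and self-completion may already be the practice.

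**Conclusion.** The concern holds in a limited form. The design does not secure the participant blinding that the article states. Participants, especially in the intervention arm, can probably infer their allocation, so blinding cannot be relied on to protect self-reported diet, physical activity and health literacy. The unblinded deliverer/assessor gives these outcomes no second line of protection.

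The conclusion rests on the visible content of the arms and on the judgement that recipients would recognise it. The size of any resulting bias is unknown. The feasibility records and the laboratory results are not exposed to this reporting bias. The correction is worth making because it is cheap and because the affected outcomes may feed the design of the next trial.

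**What to change.** 1. In Counterbalancing for confounding factors and bias, and to match in Blinding and allocation concealment, replace the single-blind statement with: participants are not told their allocation but may infer it; the deliverer/assessor is unblinded; only the data analyst is masked.
2. Extend the admitted performance and detection bias to participant reporting.
3. Have participants complete the diet, activity and health-literacy questionnaires themselves at the start of each follow-up visit, before discussion with the researcher, if this is not already done.
4. Label preliminary effects and effect sizes on these outcomes as unblinded self-report, to be read beside the laboratory-measured lipids and HbA1c.
5. Optionally, note that HLQ scale 1 may partly reflect the study contact itself.

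The cost is a few sentences and the order of tasks at the visit; no extra participants, staff or visits are needed. The downside is a weaker claim for the lifestyle outcomes.
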